## Abstract

**Background:**

Primary insomnia often corresponds to the syndrome of liver depression and spleen deficiency in traditional Chinese medicine. This study evaluates a new acupuncture protocol derived from the “Jing Bie” theory. Tianrong (TE16) and Tianyou (SI17) were selected to regulate the Shaoyang meridian, soothe the liver, regulate qi (the basic life energy or life force to maintain the physiological function of the body according to traditional Chinese medicine), strengthen the spleen, and tranquilize the mind, so as to restore sleep.

**Objective:**

The objective of this study is to evaluate the clinical efficacy of this regimen and to explore its effects on autonomic nervous system function and central nervous system chemistry.

**Methods:**

This is a single-blind randomized controlled trial. A total of 96 patients with primary insomnia (liver depression and spleen deficiency pattern) will be recruited and randomly assigned to the treatment group or the control group. At the same time, 48 healthy volunteers will be recruited as the healthy control group.

**Results:**

This study was funded in November 2023. Recruitment and data collection began in January 2024 and are currently underway. As of December 2025, a total of 40 participants have been enrolled, of whom 4 have withdrawn. Recruitment is projected to conclude by December 2026. Data analysis will be performed after the completion of recruitment. The results are expected to be published in summer 2027.

**Conclusions:**

This study integrates a traditional Chinese medicine framework with modern physiological measurements. The aim is to provide evidence for targeted acupuncture strategies by linking clinical improvement to autonomic nervous system balance and neurochemical changes and to elucidate potential mechanisms to provide a nondrug treatment option for insomnia.

## Introduction

Insomnia is a subjective experience in which patients are not satisfied with the length and/or quality of sleep, and it affects their daytime social function [1]. Long-term insomnia can lead to fatigue, mood swings, and cognitive impairment [2]. Studies have shown that acupuncture is effective in treating insomnia [3]. “Jing Bie” is a longitudinal branch of the 12 meridians, which goes deep into the body cavity to strengthen the connection between the 2 meridians in the deep part of the trunk. The theory of Jing Bie is recorded in “Lingshu · Jing Bie,” and the distribution characteristics of Jing Bie are “leaving, entering, leaving and combining.” Six acupoints, such as Tianrong (TE16) and Tianyou (SI17), are located in the neck [4]. In the theory of traditional Chinese medicine (TCM), Jing Bie not only strengthens the close relationship between the limbs and the viscera, the head, and the 5 sense organs but also plays a role in connecting the 2 meridians, reconciling the “ying” and “wei,” and promoting the balance of qi (the basic life energy or life force to maintain the physiological function of the body) and blood in the head [5]. From the perspective of modern medical anatomy, the 6 acupoints on the neck are mostly located near the sternocleidomastoid muscle, where the superior cervical ganglion and stellate ganglion of the sympathetic trunk are deeply distributed. Intervention in these parts can regulate sympathetic and parasympathetic nerve function and relieve symptoms related to autonomic nervous system (ANS) disorders. For example, stellate ganglion block (SGB) is often used clinically to treat sympathetic-parasympathetic imbalances such as migraine, cluster headache, and insomnia [6,7]. SGB can inhibit central and peripheral activity; jointly control the glands, blood vessels, and muscle movement in the region; and regulate sympathetic nerve activity from a pathologically hyperactive state to normal levels and maintain stability. Repeated SGB can interfere with autonomic nerve activity, thereby modifying autonomic nerve function [8,9]. Therefore, the acupoints selected based on the Jing Bie theory may also have a good effect on autonomic nerve regulation because they are anatomically adjacent to the stellate ganglion.

A study that analyzed the effects of acupuncture on the ANS showed that acupuncture can reduce sympathetic nerve activity under stress conditions and balance the ANS [10]. In a review that included 14 studies on the effects of acupuncture on heart rate variability (HRV), it was reported that acupuncture can reduce the low-frequency power (LF) and the LF to high-frequency power (HF) ratio (LF/HF) in patients and may function to balance the sympathetic and parasympathetic nervous systems [11]. A previous study by the project leader found that acupuncture at the acupoints Tianrong (TE16) and Fengchi (GB20) can improve the autonomic nerve function of patients with migraine. Although studies have shown that acupuncture has a regulatory effect on autonomic nerves, there is still a lack of in-depth discussion on the mechanism [12]. At present, most studies on acupuncture treatment of insomnia do not strictly distinguish TCM syndromes, and it is difficult to accurately provide effective treatment options for specific syndromes. This study focuses on insomnia of liver depression and spleen deficiency type. It is expected to clarify the curative effect of acupuncture on insomnia of this type through rigorous randomized controlled trials (RCTs) and provide more targeted evidence for clinical treatment with TCM.

HRV reflects the functional status of sympathetic and parasympathetic nerves, which offers a window into the functional status of human ANS [13]. Therefore, it is believed that HRV reflects the mechanism of excessive arousal from the changes in autonomic nerve function, and improving HRV indices and reducing excessive arousal may be a new idea for the treatment of insomnia. We designed this study based on the theory of Jing Bie selection to explore the treatment of insomnia through the analysis of HRV.

In “Huangdi Neijing,” there is a discussion on the disharmony between ying and wei in insomnia. According to the theory of branches of 12 meridians, selection of acupoints on the neck can regulate the qi of the 2 meridians; the theory also explains the principle of ANS intervention from the perspective of modern medicine. Acupuncture intervention can regulate autonomic nerve function. In a preliminary study on autonomic nerve intervention in migraine, we found that acupuncture at neck acupoints has a certain therapeutic effect. In modern medical research, HRV, which reflects autonomic nerve function, can well reflect the clinical situation of patients with primary insomnia-hyperarousal, and it is believed that primary insomnia can be treated by improving HRV indices. Therefore, in this study, we aim to examine whether, according to the theory of meridian acupoint intervention, the curative effect of the treatment of primary insomnia can be improved through autonomic nerve intervention.

## Methods

### Study Setting and Design

This study is a single-center, prospective, single-blind RCT. A total of 96 patients with primary insomnia of liver depression and spleen deficiency type will be recruited from the Department of Acupuncture and Moxibustion of the Third Affiliated Hospital of Zhejiang Chinese Medical University in Zhejiang province, China. Participants will be randomly assigned (1:1) to the acupuncture group based on the theory of Jing Bie selection or the conventional acupuncture control group. The intervention will be carried out for 4 weeks, followed by follow-up.

The specific follow-up arrangement will be evaluated in the fourth week of the treatment period, and the patients’ recovery and treatment efficacy will be assessed in depth at key follow-up time points. In both groups, the treatment will be administered 3 times a week for 4 weeks. At the same time, 48 healthy volunteers without sleep disorders will be included as the healthy control group without any intervention measures, which will be used to compare and analyze the changes in relevant indicators to evaluate the effect of acupuncture treatment more comprehensively. The flowchart of the study process is shown in Figure 1, and the trial schedule of enrollment, treatments, and assessments is displayed in Table 1. The reporting of this study protocol conforms to the SPIRIT (Standard Protocol Items: Recommendations for Interventional Trials) guidelines (Checklist 1).

**Figure 1. F1:**
[figure not shown]
Study flowchart. DBAS-16: 16-item Dysfunctional Beliefs and Attitudes About Sleep scale, GABA: γ-aminobutyric acid, Glu: glutamic acid; HRV: heart rate variability; ISI: Insomnia Severity Index; MRI: magnetic resonance imaging; PSG: polysomnography; PSQI: Pittsburgh Sleep Quality Index; SF-36: 36-item Short Form Health Survey.

**Table 1. T1:** Schedule of study assessments and outcome measures.

Research stage	Before treatment	Treatment stage	Follow-up stage
Assessment	First	Second	Third
Time (weeks)	0	4	8
Informed consent	✓	—^a^	—
Inclusion/exclusion criteria	✓	—	—
Demographic data	✓	—	—
Vital signs	✓	—	—
Medical history record	✓	—	—
Physical examination	✓	—	—
Medication situation	✓	—	—
Indicator of mechanism			
HRV^b^	✓	✓	✓
PSG^c^	✓	✓	✓
MRI^d^	✓	✓	—
Primary outcome indicator			
PSQI^e^	✓	✓	✓
SF-36^f^	✓	✓	✓
Secondary outcome indicator			
ISI^g^	✓	✓	✓
DBAS-16^h^	✓	✓	✓
GABA^i^	✓	✓	—
Glu^j^	✓	✓	—
Safety evaluation	✓	✓	✓

a Not applicable.

b HRV: heart rate variability.

c PSG: polysomnography.

d MRI: magnetic resonance imaging.

e PSQI: Pittsburgh Sleep Quality Index.

f SF-36: 36-item Short Form Health Survey.

g ISI: Insomnia Severity Index.

h DBAS-16: 16-item Dysfunctional Beliefs and Attitudes About Sleep scale.

i GABA: γ-aminobutyric acid.

j Glu: glutamic acid.

### Participant Recruitment

Participants in this study will be recruited from the outpatient Department of Acupuncture and Moxibustion of our hospital, through posters placed on the hospital’s announcement board and other ways. The recruitment information will detail the research content, purpose, process, and corresponding contact information.

The participants will be asked to first contact the research assistant for preliminary screening. Participants who may be eligible will be registered, and a specialist will be appointed to check whether they meet the inclusion and exclusion criteria of this study (Textbox 1). Only patients who meet all the inclusion criteria and do not meet any exclusion criteria will be invited to participate in the study, and they will be given a detailed introduction to the specifics of this RCT. All participants are required to sign informed consent forms and provide comprehensive personal information.

Textbox 1.Inclusion and exclusion criteria.
**Inclusion criteria**
Patients with symptoms in line with the diagnostic criteria of insomnia of liver depression and spleen deficiency type in traditional Chinese medicinePatients with symptoms in line with the western diagnostic criteria for insomnia [14]Male or female patients aged 18 to 40 yearsPatients with a disease course of more than 2 weeks
**Exclusion criteria (patients who meet any one of the following criteria will be excluded)**
Patients with insomnia caused by a variety of organic diseases or neurological or psychiatric disordersPregnant or lactating patients or those with a drug allergyPatients with more serious primary diseases such as cardiovascular and cerebrovascular diseases, gastrointestinal diseases, endocrine system diseases, or psychiatric disordersPatients with coagulation dysfunction and bleeding tendency

The baseline assessment will be performed by the same physician, and the results will be recorded in detail in the case report form. All participants will receive treatment for 4 weeks and undergo follow-up observation after treatment. The evaluation will be done at 3 time points: before treatment, after 4 weeks of treatment, and at 4 weeks after end of treatment. Each participant will receive a schedule of treatment dates and a schedule of follow-up appointments developed by research assistants who will be blinded to the grouping information.

In addition, all participants will be required to keep a sleep diary throughout the treatment and follow-up periods, recording the date of each insomnia episode, the length of time required to fall asleep, the number of times they wake up at night, the difficulty of falling asleep again, and the subjective feelings after waking up in the morning. Moreover, they will be asked to include sleep-related details as well as the name, dose, and time of use of other drugs (such as sleeping pills) during the trial and their own feelings after taking the drug.

### Ethical Considerations

The study was approved by the Medical Ethics Committee of the Third Affiliated Hospital of Zhejiang Chinese Medical University (approval no. ZSLL-KY-2024-032-01). If the main protocol needs to be modified, all members of the research team will participate in the process and submit the final modified protocol to the Medical Ethics Committee for review. This approval ensures that the study adheres to ethical standards and protects the rights and safety of participants. Patients and/or the public were involved in the design, conduct, reporting, or dissemination plans of this research. All participants are required to provide written informed consent to participate in this study. The consent process explicitly emphasizes the voluntary nature of participation and the right to withdraw at any time without penalty. To ensure privacy, all study data will be deidentified for analysis, with personal information stored separately under strict access controls. No financial compensation will be provided to participants.

To ensure successful blinding, acupuncture will be performed for patients from both groups using several common approaches: skin sterilization with 75% alcohol; usage of disposable and sterile steel needles (1.5-inch needle, 0.25×40 mm); and insertion of needles into the skin to a depth of 10 to 15 mm, left for 30 minutes. Acupuncture treatment will be performed 3 times a week, and a total of 12 acupuncture or conventional acupuncture operations will be performed in 4 weeks. In addition, the external conditions such as the nursing process and the environment during the treatment will be kept consistent for the 2 groups of patients, so as to minimize the interference of additional factors on the results of the study.

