#### Acupuncture Group

This group will include 48 patients. The patients will be placed in a supine position. Acupuncture will be performed bilaterally at Tianrong (SI17) points, with the needle inserted backward obliquely at 45±5° to a depth of 1.0 to 1.5 inches, reinforcing and reducing horizontally, and the needle insertion will be stopped when the patient feels a heat sensation in the auricle.

Acupuncture will be performed bilaterally at Tianyou (TE16) points, with the needle pointing toward the tip of the nose. The needle will be inserted to a depth of 0.5 to 1.0 inch using flat reinforcing and reducing maneuvers, until the sense of soreness and distension obviously stops; the needle will be retained for 30 minutes. The location of acupuncture points is shown in Table 2.

**Table 2. T2:** Acupoint selection and stimulation parameters for the acupuncture group.

Acupoint	Location	Manipulation
Tianyou (TE16)	On the lateral side of the neck, located in the depression at the posterior border of the sternocleidomastoid muscle, level with the mandibular angle.	The needle is directed toward the tip of the nose, the insertion depth is 0.5‐1.0 inch, the reinforcing and reducing maneuvers are flat, needle insertion is stopped when soreness is obvious, and the needle is retained for 30 min.
Tianrong (SI17)	In the lateral aspect of the neck and in the depression on the anterior border of the sternocleidomastoid muscle and posterior to the mandibular angle	The needle is inserted backward obliquely at 45±5° to a depth of 1.0‐1.5 inches, with reinforcing and reducing maneuvers, and needle insertion is stopped when the patient feels a heat sensation in the auricle.

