#### Control Group

This group will include 48 patients. The patients will be placed in a supine position. Acupuncture will be performed at Baihui (DU20), Sishencong (EX-HN1), bilateral Qimen (LR13), Zhangmen (LR14), Hegu (LR14), and Taichong (LR3), with reinforcing and reducing maneuvers. The needle insertion will be stopped when acid swelling is obvious, and the needle will be retained for 30 min. The location of acupuncture points is shown in Textbox 2.

Textbox 2.Acupoint selection and stimulation parameters for the control group.

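### The 10–15 mm needle depth said to be common to both groups cannot be reconciled with the depth specified at Tianrong in the acupuncture group, and overlaps only narrowly with that at Tianyou

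*Protocol article*

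**What the plan says.** **Common depth.** The section Randomization and Blinding introduces a list of shared features: "To ensure successful blinding, acupuncture will be performed for patients from both groups using several common approaches". The list includes the needle, described as "usage of disposable and sterile steel needles (1.5-inch needle, 0.25×40 mm", and the depth, "insertion of needles into the skin to a depth of 10 to 15 mm, left for 30 minutes".

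**Acupuncture group.** The Acupuncture Group section gives separate depths for the two neck points, and Table 2 repeats them. At Tianrong the instruction reads "with the needle inserted backward obliquely at 45±5° to a depth of 1.0 to 1.5 inches". At Tianyou it reads "The needle will be inserted to a depth of 0.5 to 1.0 inch".

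**Control group.** The Control Group section and Textbox 2 give point names, locations, manipulation and retention time, but no depth. The 10–15 mm in Randomization and Blinding is the only depth stated for this arm.

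**Point codes.** The Abstract has "Tianrong (TE16) and Tianyou (SI17) were selected to regulate the Shaoyang meridian", and the Introduction uses the same pairing. The Acupuncture Group section and Table 2 reverse it, for example "Acupuncture will be performed bilaterally at Tianrong (SI17) points". The Control Group section has "Zhangmen (LR14), Hegu (LR14", so LR14 appears twice, while Textbox 2 codes Hegu as LI4.

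**The concern.** One section gives a single depth for all needling in both arms. Another gives point-specific depths for one arm, in a different unit. Once converted, the two do not agree.

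Three things depend on this.

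- **Delivery and safety.** The points are in the neck. Two stated depth rules that cannot both be followed at one of them are a safety matter as well as a matter of consistency.
- **Blinding.** Equal depth is offered as one of the measures that keep the arms alike for the participant. If the acupuncture arm is needled as its own section specifies, that measure is not in place there.
- **Attribution.** The Introduction and Discussion rest the proposed mechanism on the closeness of these points to the cervical sympathetic ganglia. Depth is thus part of what the trial sets out to test, and a reader of the results needs to know which depth was used.

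**Working it through.** **Inputs, all from the protocol article**

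- Common depth: 10–15 mm (Randomization and Blinding).
- Needle: 1.5 inches, 40 mm long (same section). This gives the document's own scale: 40 / 1.5 = 26.7 mm per inch.
- Tianrong: 1.0–1.5 inches at 45±5°, that is 40–50° (Acupuncture Group; Table 2).
- Tianyou: 0.5–1.0 inch (Acupuncture Group; Table 2).
- Standard inch: 25.4 mm.

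**Step 1. Convert and compare with 10–15 mm**

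Depth in mm = depth in inches × mm per inch.

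| Point | Scale | Range in mm | Overlap with 10–15 mm |
|---|---|---|---|
| Tianrong | 25.4 | 25.4–38.1 | none |
| Tianrong | 26.7 | 26.7–40.0 | none |
| Tianyou | 25.4 | 12.7–25.4 | 12.7–15 |
| Tianyou | 26.7 | 13.3–26.7 | 13.3–15 |

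**Step 2. Size of the gap at Tianrong**

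- Standard inch: 25.4 − 15 = 10.4 mm; 25.4 / 15 = 1.69.
- Needle scale: 26.7 − 15 = 11.7 mm; 26.7 / 15 = 1.78.

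The shallowest depth given for Tianrong is therefore about 1.7 to 1.8 times the deepest depth given as common to both arms.

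**Step 3. Does the oblique angle explain it?**

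Suppose 10–15 mm means depth perpendicular to the skin and the inch figures mean length along the needle. Then perpendicular depth = length × sin(angle).

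- Shallowest: 25.4 × sin 40° = 25.4 × 0.643 = 16.3 mm.
- Deepest: 38.1 × sin 50° = 38.1 × 0.766 = 29.2 mm.

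The range 16.3–29.2 mm still lies outside 10–15 mm. The larger needle scale moves it further out.

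**Step 4. Does a body-proportional inch explain it?**

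The article does not say that such a unit is meant. If it were, the lower limit at Tianrong (1.0 inch) would reach 15 mm only if an inch were 15 mm or less, against 26.7 mm on the needle scale. For the whole of 1.0–1.5 inches to lie within 10–15 mm, an inch would have to be exactly 10 mm. Tianyou would then start at 0.5 × 10 = 5 mm, below the common range. No single inch makes all three statements agree in full.

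**Step 5. Point codes, side by side**

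| Place | Tianrong | Tianyou |
|---|---|---|
| Abstract, Introduction | TE16 | SI17 |
| Acupuncture Group, Table 2 | SI17 | TE16 |

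The acupuncture instructions attach depth and direction to a point name and an anatomical location. The sections with the reversed codes contain no needling instruction. In the control arm, Textbox 2 places Hegu on the hand and Zhangmen on the lateral abdomen.

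**The case against.** The best defence is that the acupuncture arm is specified consistently where it matters. The Acupuncture Group section and Table 2 agree on point names and depth ranges, and Table 2 adds locations. The session schedule and the 30-minute retention are also stated. On this view the fault is one general sentence in the blinding section. The article also requires operators to be trained and qualified and to follow standardised procedures, and it condenses a fuller protocol that is not shown.

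Much of this stands, and it limits the point. A reader might go further in three ways that the document does not support.

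- **That the treatment as a whole is undefined.** It is not. Nothing conflicts with the control arm's single stated depth, Tianyou can be needled within both ranges at about 13–15 mm, and the other elements of the acupuncture regimen are given.
- **That the code swap changes what is done where.** Each instruction is tied to a name and a location, and both neck points are needled bilaterally in every acupuncture-group patient. The Study Rationale section assigns SI17 to the small intestine meridian and TE16 to the triple energizer, and links Tianrong to hand Taiyang and Tianyou to hand Shaoyang. These are labelling errors.
- **That all 40 participants enrolled by December 2025 were exposed to the conflict.** The article does not say how many of the 40 are untreated healthy volunteers, and patients are allocated 1:1, so only about half of those randomized would be in the affected arm.

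Nor does the document show that depth has in fact varied between operators or that anyone was harmed.

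The defence does not remove the contradiction. The common-depth sentence names both groups and offers equal depth as a blinding measure. Training and standard procedures cannot settle which of two written rules applies. A full protocol might state the depth correctly, but this text would still be wrong.

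**Conclusion.** The point holds for needle depth in the acupuncture arm. At Tianrong the two stated ranges are disjoint: the gap is 10.4 mm on the standard inch and 11.7 mm on the document's own needle scale, and the ranges stay apart if the common depth is read as perpendicular depth at 40–50°. At Tianyou they share only 12.7–15 mm (13.3–15 mm on the needle scale). The statement that depth is common to both groups is therefore not true of the acupuncture arm as specified.

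The conclusion assumes that the inch is the standard one or the one implied by the needle; the article offers no other. It does not touch the sample size. It takes no view on which depth is right. The code inconsistencies are an editorial matter and carry no weight in this conclusion.

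**What to change.** 1. The responsible clinicians should reconcile the depth in Randomization and Blinding with the Acupuncture Group section and Table 2, and state depth in a single unit throughout.
2. Correct or remove the common-depth statement in Randomization and Blinding so that it matches the reconciled text.
3. Confirm from treatment records, where available, the depth used in acupuncture-group patients already treated, so that the report can describe what was delivered.
4. As an editorial correction, make the point codes consistent: Tianrong and Tianyou in the Abstract and Introduction against the Acupuncture Group section and Table 2, and the duplicated LR14 in the Control Group section against LI4 for Hegu in Textbox 2.

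The cost is a protocol correction, submitted to the ethics committee by the route the article describes if it counts as a modification, a note to the operators, and a check of existing records. Recruitment is planned to run to the end of 2026, so a prompt correction would still cover the remaining patients.
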